## Abstract

**Background:**

For the surgical treatment of recurrent primary spontaneous pneumothoraces (rPSP) different operative therapies are applied to achieve permanent freedom from recurrence.

**Methods/design:**

This multicenter clinical trial evaluates the long-term results of two commonly applied surgical techniques for the treatment of rPSP. Based on the inclusion and exclusion criteria, and after obtaining the patients’ informed consent, participants are randomized into the two surgical treatment arms: pulmonary wedge resection plus parietal pleurectomy (WRPP) or parietal pleurectomy alone (PP). Consecutively, all study participants will be followed up for two years to evaluate the surgical long-term effect. The primary efficacy endpoint is the recurrence rate of pneumothorax within 24 months after surgery. The calculated sample size is 360 patients (*n* = 180 per treatment arm) to prove superiority of one of the two treatments. So far, 22 surgical sites have submitted their declaration of commitment, giving the estimated number of participating patients.

**Discussion:**

A prospective randomized clinical trial has been started to compare two established surgical therapies to evaluate the long-term results regarding recurrence rates. Furthermore, cost of treatment, and influence on the perioperative morbidity and mortality as well as on quality of life are analyzed. If the study reveals equivalence for both surgical techniques, unnecessary pulmonary resections could be avoided.

**Trial registration:**

ClinicalTrials gov: NCT01855464, 06.05 2013.

**Electronic supplementary material:**

The online version of this article (doi:10.1186/s13063-015-1060-z) contains supplementary material, which is available to authorized users.

## Background

### Rationale

A pneumothorax (PTX) is an accumulation of air in the pleural space between the lung and chest wall [1]:A **primary pneumothorax** (pPTX) occurs in healthy individuals without pre-existing lung disease and without previous thoracic intervention or chest injury.A **secondary pneumothorax** is usually the result of an underlying lung disease (for example, pulmonary emphysema) or a previous intervention (such as pleural puncture) or a thoracic trauma (both blunt and penetrating).

pPTX represents a common disease in industrialized countries with an annual incidence of 18–28 per 100,000 [2, 3]. The goal of surgical pneumothorax treatment is full re-expansion of the collapsed lung parenchyma and recurrence prevention. Varying surgical strategies are followed to achieve these targets. Thoracoscopic parietal pleurectomy is the most frequently used surgical technique. The benefit of additional resection of the pulmonary apex, however, is still questionable [4, 5]. A theoretical advantage might be a stronger adhesion between the stapled apex of the lung and the chest wall (for example, in the sense of a foreign body reaction), which could be accompanied by a lower recurrence rate. On the other hand, the use of stapling devices for pulmonary wedge resection increases surgical costs and the risk of postoperative bleeding and parenchymal fistulas, translating into longer hospital stays. However, both surgical strategies are routinely applied in Germany’s specialized thoracic surgery units. While their published short-term postoperative results seem to be comparable, long-term results are still missing. Furthermore, the associated perioperative morbidity and mortality and the postoperative quality of life have not been evaluated so far. In a recent observational study, it has been shown that up to 45 % of patients after operative therapy have recurrent and occasionally persistent postoperative symptoms such as scar pain and paresthesia [6]. Until now there has been no prospective randomized clinical trial on this topic. Retrospective cohort analyses describe both methods as equivalent [7]. The rationale of the study protocol for this prospective randomized multicenter study was to evaluate whether pulmonary wedge resection in combination with a partial apical pleurectomy (WRPP) is superior to the partial apical pleurectomy alone (PP) for treatment of recurrent pPTX.

## Methods/design

### Hypothesis

The WOPP (Wedge Resection or Parietal Pleurectomy for the Treatment of Recurrent Pneumothorax) study is a two-arm, prospective, randomized, nationwide multicenter clinical study in thoracic surgery, which was designed to test the hypothesis of whether partial pleurectomy for the treatment of recurrent primary pneumothorax alone is inferior compared to an additional wedge resection regarding the recurrence rate over two years.

### Inclusion and exclusion criteria

All patients between 15 and 40 years of age with recurrent pPTX and patients who have a therapy refractory first event of a pneumothorax are included. A treatment-resistant first event of a pneumothorax is considered to be a pPTX treated by insertion of a chest tube and PTX recurrence following chest tube removal during the same hospital stay. Excluded are patients with existing pulmonary fistula, patients with known underlying lung disease, and patients who have already undergone surgical or interventional pleurodesis or ipsilateral thoracic surgery. The latter does not include previously inserted chest tubes. The presence of single or multiple small or large bullae in the preoperative imaging or during thoracoscopy does not represent an exclusion criterion for patients.

### Ethical approval statement

The ethics committees of the University of Würzburg and all participating centers have approved the study protocol. A list of all ethical bodies that approved this study is provided in Additional file 1.

### Randomization

To prevent selection bias and insure against accidental bias, we will allocate patients to the treatment groups by randomization. In this way we can expect to get comparable study groups regarding observed and unobserved confounders.

Patients who are suitable after verification of the inclusion and exclusion criteria will be thoroughly informed about the WOPP study by a study physician. After approval of the study and submission of the written informed consent, patients are randomized. Randomization is done electronically via a web-based software tool (SecuTrial, interActive Systems GmbH, Berlin, Germany). We chose an allocation ratio of 1:1 because it maximizes statistical power for a given total sample size and there are no ethical or practical objections to this ratio. To minimize random error, 750 patients are to be screened and 360 patients (*n* = 180 per arm) will be randomized. Twenty centers have declared their participation in the study. The study design is shown in Fig. 1.

**Fig. 1 Fig1:**
[figure not shown]
Course of the WOPP trial

### Blinding

Blinding of the patient and the surgeon after randomization is not meaningful because staple lines after pulmonary wedge resection can often be seen on postoperative chest X-rays.

### Endpoints

The primary endpoint is PTX recurrence within the first 24 months after operative treatment. PTX recurrence is defined as postoperative lung collapse documented by chest X-ray. Secondary endpoints are morbidity, mortality, and postoperative convalescence. Morbidity will be differentiated between general and surgical complications. In addition, postoperative pain (at rest/under exertion) will be determined by the visual analogue scale (VAS). Postoperative quality of life will be captured by using the SF-36 questionnaire.

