### Sample size estimation

The sample size calculation is based on the primary endpoint PTX recurrence within the first 24 months. We will test the null hypothesis of equal underlying population proportions for PTX recurrence for patients treated with pPTX alone and patients treated by WRPP by using a two-sided Fisher’s exact test at significance level 0.05.

Our assumptions for calculating the sample size are based on Czerny et al. [7]. Conservatively we assume underlying PTX recurrence proportions of 8.6 % for patients under pPTX and 1.4 % for patients under WRPP, a difference of 7.2 %. Sample sizes of 170 for both groups ensure a power of 80 % to detect this difference as a significant deviation from the null hypothesis of equal PTX recurrence proportions for both treatment strategies. Due to the visits without painful procedures and the comparatively young and healthy study population, we assume a low drop-out rate of 5 %. Therefore, 2*180 = 360 patients are to be included in the study at the beginning. PASS 11, developed by NCSS Statistical Software, Kaysville, UT, USA, was used for sample size calculation.

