### Study procedure

All patients with pPTX recurrence or a refractory first event will be screened for study participation. For each potential study participant the inclusion and exclusion criteria will be checked by a study physician. After providing informed consent, the participant will be randomized in one study group.

The baseline pain level and the quality of life are determined using the SF-36 questionnaire and the VAS score prior to any other study intervention in all participants. The standard treatment is parietal pleurectomy alone (control arm), and the validating therapy is the parietal pleurectomy in combination with an additional apical pulmonary wedge resection (experimental arm). All surgeries are performed by video-assisted thoracoscopy under general anesthesia and include a parietal pleurectomy for PTX treatment. Additionally, in the experimental group an apical pulmonary wedge resection is performed. The postoperative treatment is carried out according to the respective hospital standard. Perioperative variables like morbidity, mortality, subjective pain, duration of chest tube, surgical reintervention, and length of hospital stay will be determined. To assess the long-term effect of surgical intervention, all patients will be followed up for two years. The examinations for the individual follow-up visits are listed in Table 1.

**Table 1 Tab1:** Overview of the study-related examinations

	Pre-OP	Intra-OP	Station	Follow-up		
Visit	V1		V2	V3	V4	V5
Week/month	OP-X		7. post OP day or day of discharge	6 months	12 months	24 months
Inclusion/exclusion criteria	X					
Consent	X					
Demographic data	X					
Medical history	X					
Smoking	X		X	X	X	X
Physical examination	X					
Chest X-ray^a^	X					
Pain level (VAS)	X		X	X	X	X
Quality of life (SF-36, German version)	X		X	X	X	X
Vanderschueren classification		X				
Postoperative complications			X	X		
AEs/SAEs			X	X	X	X
Duration of hospital stay			X	X		
Material costs^b^						X

^a^In case of pregnancy of a study participant, the chest X-ray will be replaced by a chest ultrasound

^b^At the end of the operation, the number of used trocars and stapling magazines will be documented

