### Dropout/exclusions

The termination criteria of the study are defined as thoracic reintervention (for example, drainage system, thoracentesis with suction, surgery due to recurrence or other indication), the patient’s desire to withdraw from the current study, and violation of the protocol. During the hospital stay after surgery (and thus after randomization) a new or additional chest tube is not a termination criterion. Also, a pleural puncture for aspiration of pneumothorax or residual pneumothorax is not a termination criterion. Reoperation during the hospital stay after the initial procedure with the need for a parenchymal resection (for example, due to a recurrence pneumothorax or fistula formation) will cause the exclusion of the patient from the study. Patients may cancel their participation in the study at any time they wish, without giving reasons for the decision. In addition, the principal investigator may exclude a patient from the study if the continuation of the study compromises the patient’s well-being. The study cancellation will be documented in the eCRF and in the patient’s file, and all SAEs occurring from this point must be followed up. Premature discontinuation of the entire study will be done at the recommendation of the DSMB that the study be terminated for security reasons.

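### The primary-event rule names no side, does not separate residual air from a new pneumothorax, and does not fit the exclusion rule, the visit schedule or the imaging footnote

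*Protocol article*

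**What the plan says.** **Event and window.** Endpoints: "The primary endpoint is PTX recurrence within the first 24 months after operative treatment", followed by "PTX recurrence is defined as postoperative lung collapse documented by chest X-ray". No side, no condition that the lung had first re-expanded, and no imaging other than chest X-ray is named.

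**In-hospital events.** Dropout/exclusions says "During the hospital stay after surgery (and thus after randomization) a new or additional chest tube is not a termination criterion" and "Also, a pleural puncture for aspiration of pneumothorax or residual pneumothorax is not a termination criterion". The sentence after these takes a patient out of the study if an in-hospital reoperation needs a parenchymal resection, and gives recurrent pneumothorax as one example of the cause.

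**Analysis set.** Statistical analysis takes as the primary set all randomized patients in whom diagnostic thoracoscopy confirmed that a thoracoscopic operation is feasible. It does not remove patients who are later reoperated.

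**Schedule.** Table 1 (Study procedure) has one chest X-ray mark, at V1 before surgery. None of its rows is for recurrence. Footnote a reads: "In case of pregnancy of a study participant, the chest X-ray will be replaced by a chest ultrasound".

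**Planning figures.** Sample size estimation uses a "two-sided Fisher’s exact test at significance level 0.05", 8.6% "for patients under pPTX and 1.4 % for patients under WRPP, a difference of 7.2" percentage points, and states: "Sample sizes of 170 for both groups ensure a power of 80 % to detect this difference". The label pPTX there evidently means the pleurectomy-alone arm (PP).

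**The concern.** The trial asks whether adding a wedge resection changes recurrence after an operation on one lung. A collapse of the other lung says nothing about that. Air left on an early postoperative film is not clearly a recurrence either. A rule that does not settle these two cases leaves the decision to each site, in a trial where patients and surgeons know the allocation.

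The second problem is loss of events. If a patient leaves the study because of an early recurrence, and follow-up or analysis stops there, a primary event can disappear from a set that is meant to keep everyone whose operation was feasible.

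The plan expects few events, so a handful of classification decisions could change the result.

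**Working it through.** **1. The plan's own figure.** Inputs from Sample size estimation: p1 = 0.086 (PP), p2 = 0.014 (WRPP), d = 0.072, two-sided alpha 0.05, power 0.80. The mean rate is 0.050.

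- Without continuity correction: n0 = [1.96·√(2·0.05·0.95) + 0.8416·√(0.086·0.914 + 0.014·0.986)]² / 0.072² = 142.7, so 143 per arm.
- With continuity correction: n = (n0/4)·[1 + √(1 + 4/(n0·d))]² = 169.3, so **170 per arm**, as stated.
- Dropout: 170/0.95 = 178.9, so 179 per arm and 358 in total. The plan rounds to 360.
- Full enumeration of the two-sided Fisher test at 170 per arm gives power **84.7%**. The stated 80% is therefore conservative, and the sample size contains no arithmetic error.

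**2. How few events decide the trial.** Expected counts are 170·0.086 = 14.6 and 170·0.014 = 2.4. With 170 per arm, 10 v 2 events gives Fisher p = 0.035 and 9 v 2 gives p = 0.061. One reclassified patient can move the result across 0.05.

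**3. Unrelated events, equal in both arms (illustration).** The documents give no rate, so c is assumed. Counted rate: p' = p + c(1 − p).

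| c | PP | WRPP | Exact Fisher power, 170 per arm |
|---|---|---|---|
| 0 | 8.6% | 1.4% | 84.7% |
| 1% | 9.5% | 2.4% | 75.6% |
| 2% | 10.4% | 3.4% | 67.6% |
| 3% | 11.3% | 4.4% | 60.5% |
| 5% | 13.2% | 6.3% | 49.7% |

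**4. Unrelated events, unequal between arms (illustration).** The Background says that stapling raises the risk of parenchymal fistulas, so early air could fall more on WRPP. With the same formula applied to WRPP only, power is 65.1% at c = 1% and 44.6% at c = 2%. Applied to PP only at c = 1% (9.5% v 1.4%), power rises to 90.9%. The direction therefore depends on which arm has the extra events.

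**5. Events lost through exclusion (illustration).** If the expected PP count of 14.6 falls by 1, 2 or 3 events, power is 79.2%, 72.4% or 64.5%. That such losses would fall mainly on PP is an assumption. The documents give no rate.

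**6. The sections side by side.**

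- *Endpoints and Statistical analysis against Dropout/exclusions.* A patient with an in-hospital recurrence seen on X-ray and treated by reoperation with resection meets the event definition and belongs to the primary set, yet is excluded from the study. These statements conflict.
- *Endpoints against the chest tube and aspiration sentences.* Those sentences decide who stays in the study. A patient can stay and also be an event, so there is no contradiction. They do name residual pneumothorax alongside pneumothorax, a distinction that the endpoint does not make.
- *Inclusion and exclusion criteria against Endpoints.* For entry with a refractory first event, recurrence is tied to removal of the chest tube. The endpoint has no comparable anchor.
- *Endpoints against Table 1.* The endpoint needs a film, and none is scheduled after surgery. The adverse-event list in the safety section does not name pneumothorax. A recurrence therefore reaches the AE/SAE row through a criterion such as re-operation or hospitalization, or through another listed event.
- *Endpoints against footnote a.* Ultrasound may replace the X-ray in pregnancy, but an ultrasound finding does not satisfy the definition.

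**The case against.** The strongest reply is that this is a condensed article. The centers hold the full protocol and an eCRF exists, so side, date and imaging fields may be specified there. Recurrence after a one-sided operation is naturally read as same-side. Monitoring treats primary outcomes as core data for every patient, re-operation and hospitalization are SAEs, and the Blinding section presupposes postoperative films. Recurrences are therefore not simply uncollected.

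Much of this stands. It limits the point to ambiguity and poor fit between sections, and does not show that sites lack a working rule. It does not remove the point, because the event rule is printed as a definition and the exclusion rule conflicts with it as printed.

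Three stronger readings are tempting, and the document does not support them:

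- *That the endpoint has no starting point.* The window opens at the operation. What is missing is a condition that makes a later collapse a new event.
- *That contralateral collapse and residual air definitely count.* This follows from the literal wording, but the article nowhere says it.
- *That the chest tube and aspiration sentences contradict the endpoint.* They are termination rules only.

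It is also fair to object that the background rates are assumed and that equality between arms is doubtful for early air leaks. The power figures show sensitivity. They do not predict a loss.

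**Conclusion.** The point holds as a badly fixed primary-event rule. The definition lacks a side and a rule for residual air. It conflicts directly with the exclusion after in-hospital reoperation, and it is not matched by the visit schedule or the ultrasound footnote. The sample size itself reproduces.

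The size cannot be estimated from the documents. Under an assumed equal background of 1% to 5%, exact power at 170 per arm would be 75.6% to 49.7% instead of 84.7%. If the extra events differ by arm, power and the estimated difference could move either way. The importance rests on the small expected counts, about 14.6 v 2.4, and on unblinded ascertainment through unscheduled films.

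**What to change.** - State one event definition: pneumothorax on the operated side, a rule separating residual air from a new event, and the accepted imaging including the ultrasound substitution. Use it in Endpoints, Statistical analysis, Table 1 and Dropout/exclusions.
- The sponsor must set the residual-air rule. An anchor such as drain removal comes after randomization and may differ by arm, so the choice should be justified and must not drop in-hospital recurrences.
- Record contralateral pneumothorax and residual air separately.
- Count in-hospital recurrences that lead to reoperation as primary events in the primary analysis set, and reconcile Dropout/exclusions with this. This concerns counting and analysis only. No rule for clinical management is proposed.
- Add a recurrence item (date, side, imaging) at V2 to V5. Unless follow-up films are scheduled, describe the endpoint as clinically detected, imaging-confirmed recurrence. This makes the description accurate but does not remove the unblinded ascertainment.

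**Cost.** Changes to protocol and eCRF wording, one short visit item, no added procedure, and probably slightly fewer counted events than under the literal wording. The article reports 61 of 360 patients randomized at 22 January 2015, so most patients could still be classified prospectively. Those already enrolled would need the same definition applied to their existing records.

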### Sample size estimation

The sample size calculation is based on the primary endpoint PTX recurrence within the first 24 months. We will test the null hypothesis of equal underlying population proportions for PTX recurrence for patients treated with pPTX alone and patients treated by WRPP by using a two-sided Fisher’s exact test at significance level 0.05.

Our assumptions for calculating the sample size are based on Czerny et al. [7]. Conservatively we assume underlying PTX recurrence proportions of 8.6 % for patients under pPTX and 1.4 % for patients under WRPP, a difference of 7.2 %. Sample sizes of 170 for both groups ensure a power of 80 % to detect this difference as a significant deviation from the null hypothesis of equal PTX recurrence proportions for both treatment strategies. Due to the visits without painful procedures and the comparatively young and healthy study population, we assume a low drop-out rate of 5 %. Therefore, 2*180 = 360 patients are to be included in the study at the beginning. PASS 11, developed by NCSS Statistical Software, Kaysville, UT, USA, was used for sample size calculation.

### Statistical analysis

The primary statistical analysis will be performed in the intention-to-treat (ITT) population. This analysis set includes all randomized subjects for which a diagnostic thoracoscopy has confirmed that thoracoscopic operation is feasible. We assume that the number of patients with recurrent pneumothorax after 24 months follows a binomial distribution in both groups. Within the primary analysis we will test the null hypothesis of equal proportions, which means equal probabilities for recurrent pneumothorax after 24 months for patients subject to WRPP and patients subject to PP by a two-sided Fisher’s exact test. Furthermore, a stratified analysis with the stratification factor study center will be performed using Mantel-Haenszel estimation of relative risk and testing for heterogeneity of stratum risks.

Within a secondary analysis we will calculate an adjusted odds ratio for the experimental treatment method WRPP relative to the comparing treatment PP using multiple logistic regression analysis. Secondary outcome analyses will be carried out depending on scale level and distribution and will be considered exploratory. In our analyses, 95 % confidence intervals will be calculated. The method for constructing the confidence interval in each case will depend on the type of the response variable and the variable to be tested. Controlling for potential confounders (such as age, gender, and smoking) will be performed by using multiple statistical models adjusting for these variables. Additional subgroup analyses considering gender aspects, age, and study center are planned. SAS 9.3 or corresponding subsequent SAS versions will be used for all data analyses.

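### The primary set labelled ITT drops randomised patients on a finding made after randomisation, so it is a modified ITT set and open to selection bias of unknown size

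*Protocol article*

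**What the plan says.** All references are to the protocol article.

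- **Statistical analysis**, label: "The primary statistical analysis will be performed in the intention-to-treat (ITT) population".
- **Statistical analysis**, definition in the next sentence: "This analysis set includes all randomized subjects for which a diagnostic thoracoscopy has confirmed that thoracoscopic operation is feasible".
- **Randomization**: "After approval of the study and submission of the written informed consent, patients are randomized".
- **Study procedure**: "After providing informed consent, the participant will be randomized in one study group".
- **Blinding**: "Blinding of the patient and the surgeon after randomization is not meaningful", because staple lines can show on later X-rays.
- **Inclusion and exclusion criteria**: thoracoscopic infeasibility is not listed as an exclusion. Bullae, including those seen at thoracoscopy, are expressly not one.
- **Endpoints**: recurrence is counted over 24 months from operative treatment.

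The text shown does not define feasibility, say who decides it, withhold the allocation until it is decided, or plan an analysis of all randomised patients.

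**The concern.** A patient can be eligible, consented and randomised, and then leave the primary analysis because of what is found in theatre. That is not intention to treat, whatever the label. The Randomization section justifies randomisation by the prevention of selection bias and by comparability on observed and unobserved confounders. An exclusion made after allocation gives up that protection if the decision can be influenced by the arm. The arms do differ in what has to be done, since only one includes an apical wedge resection.

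The primary test rests on few events. If patients with a different recurrence risk leave the two arms unequally, the test no longer compares the groups that randomisation formed. A reader who sees the ITT label would not know this.

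**Working it through.** **1. Order of events.** Randomization and Study procedure both place allocation after consent, and neither ties it to thoracoscopy. The definition of the set speaks of randomised subjects whose thoracoscopy confirmed feasibility, so it allows for randomised subjects in whom it did not. Feasibility is thus a post-randomisation criterion. Blinding says that the surgeon is not blinded after randomisation.

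**2. The plan's own sample size.** Inputs from Sample size estimation: 8.6% (pleurectomy alone, PP) and 1.4% (wedge resection plus pleurectomy, WRPP), a "two-sided Fisher’s exact test at significance level 0.05", 80% power, 170 per arm, 5% drop-out, 180 per arm.

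- Pooled-variance formula: n = [1.96·√(2·0.05·0.95) + 0.8416·√(0.086·0.914 + 0.014·0.986)]² / 0.072² = 142.7, rounded up to 143.
- With continuity correction, the usual approximation to Fisher's test: n′ = (142.7/4)·[1 + √(1 + 4/(142.7·0.072))]² = 169.3, rounded up to 170. This agrees with the plan.
- Drop-out: 170/0.95 = 178.9, rounded up to 179, against the stated 180. This agrees within rounding.
- Exact enumeration of Fisher's test gives 84.7% power at 170 per arm, so the plan is slightly conservative. There is no separate allowance for infeasibility.

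**3. Expected events.** 170 × 0.086 = 14.6 and 170 × 0.014 = 2.4, or about 15 v 2.

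**4. How many exclusions would matter?** Two-sided Fisher p-values, PP v WRPP:

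| Starting table | PP patients excluded | Resulting table | p |
|---|---|---|---|
| 15/170 v 2/170 | none | same | 0.0018 |
| | 2, both would recur | 13/168 v 2/170 | 0.0033 |
| | 6, all would recur | 9/164 v 2/170 | 0.033 |
| | 7, all would recur | 8/163 v 2/170 | 0.057 |
| 12/170 v 3/170 | none | same | 0.031 |
| | 2, both would recur | 10/168 v 3/170 | 0.052 |
| | 2, neither would recur | 12/168 v 3/170 | 0.018 |

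The second starting table is a chosen borderline case, not the planned scenario.

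**5. False-positive risk when there is no true difference.** Assumed, because the documents give no figures: 180 per arm, true recurrence 5% or 8.6% in both arms, exclusions from one arm only.

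| Excluded from one arm | Their recurrence risk | Shift in that arm's rate | Fisher type I error |
|---|---|---|---|
| 0 | – | 0 | 0.027–0.031 |
| 5 | 30% | 0.6–0.7 points | 0.041–0.043 |
| 9 (5%) | 50% | 2.2–2.4 points | 0.10–0.15 |

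Only the last, deliberately severe case clearly exceeds the nominal 0.05.

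**6. Power.** With all randomised patients kept and 5% drop-out (180 × 0.95 = 171 per arm), exact power is 84.9%. With all 180 per arm observed it is 87.2%. Under the present rule, with assumed infeasibility of 2%, 5% and 10% on top of drop-out, 167, 162 and 153 per arm remain, and power is 83.8%, 82.4% and 79.4%.

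**The case against.** The case on the other side concedes the label and disputes the harm. Most of it stands.

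- **Who decides, and knowing what.** A reader might infer that a surgeon who already knows the arm decides who stays in the analysis. The article does not say so. It names no judge of feasibility and does not say when the allocation reaches theatre, and its course-of-trial figure is not shown. The inference is well supported by the order of events and the absence of blinding, but it remains an inference.
- **Mechanism.** A reader might suppose that large bullae would be judged differently by arm. The eligibility section rules out bullae as a ground for exclusion, including bullae first seen at thoracoscopy. Adhesions remain possible, but the stated criterion is whether a thoracoscopic operation can be done, and both arms use the same access and the same pleurectomy. A judgement that is truly independent of the arm would cause little bias.
- **Size.** A reader might conclude from about 17 expected events that very few exclusions decide the trial. At the planned effect they do not: seven selective losses of recurring PP patients are needed. The 12 v 3 example also requires that both exclusions fall in one arm and that both patients would have recurred.
- **Direction.** Nothing in the article shows that infeasible patients have a higher recurrence risk, or that they would be lost from PP rather than WRPP.

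None of this repairs the definition. The article still contains no safeguard that makes the judgement independent of the arm, and no analysis of all randomised patients. Nor is this a detail left to an analysis plan: the article defines the primary set, and a plan that follows it inherits the definition.

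**Conclusion.** The concern holds in a limited form. The primary set is a modified ITT set under an ITT label, because it removes randomised patients on a finding made after an open allocation. It is open to selection bias; the documents do not show that bias will occur, how large it would be, or which arm it would favour.

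If the planned effect is real, a few exclusions leave the conclusion unchanged. If the true effect is smaller or absent, a handful of unequal exclusions could move a borderline result. Absence is a case that the abstract itself considers, when it speaks of the two techniques proving equivalent. The illustrations rest on assumed exclusion numbers and risks. With few or balanced exclusions the effect is small. This should be fixed before outcomes are analysed, but it does not by itself invalidate the trial.

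**What to change.** 1. **Primary set.** Define ITT as all randomised patients, analysed in the arm to which they were allocated.
2. **Time origin.** Because the endpoint runs from operative treatment, add a rule: count 24-month recurrence from the index operation. If the study operation is not done, count it from the date of the attempted procedure, or from randomisation if there was none.
3. **Sensitivity analysis.** Relabel the thoracoscopy-feasible set as modified ITT, analyse it as a sensitivity analysis, and report exclusions by arm with reasons.

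The cost is a change of wording in the protocol and analysis plan, 24-month follow-up of patients who did not get the study operation, and slight dilution of the effect from those patients. The sample size need not change (84.9% exact power at 171 per arm).

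4. **Optional.** For patients still to be recruited (61 of 360 had been randomised by 22.01.2015), the web tool could release the allocation only after feasibility has been recorded. This removes the problem at source. It also changes the randomisation process in about 20 centres during recruitment and leaves two randomisation timings in one trial, so it is not free. Items 1 to 3 suffice without it.
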